**Methods:**

The multicentre, randomized controlled E.motion trial is part of the German ProHEAD consortium (Promoting Help-seeking using E-technology for ADolescents). The objective of the trial is to investigate the efficacy and cost-effectiveness of two online interventions to reduce depressive symptomatology in high-risk children and adolescents with subsyndromal symptoms of depression in comparison to an active control group. Participants will be randomized to one of three conditions: (1) Intervention 1, a clinician-guided self-management program (iFightDepression®); (2) Intervention 2, a clinician-guided group chat intervention; and (3) Control intervention, a psycho-educational website on depressive symptoms. Interventions last six weeks. In total, *N* = 363 children and adolescents aged ≥ 12 years with Patient Health Questionnaire-9 modified for Adolescents (PHQ-A) scores in the range of 5–9 will be recruited at five study sites across Germany. Online questionnaires will be administered before onset of the intervention, at the end of the intervention, and at the six-month follow-up. Further, children and adolescents will participate in the baseline screening and the one- and two-year school-based follow-up assessments integrated in the ProHEAD consortium. The primary endpoint is depression symptomatology at the end of intervention as measured by the PHQ-A score. Secondary outcomes include depression symptomatology at all follow-ups, help-seeking attitudes, and actual face-to-face help-seeking, adherence to and satisfaction with the interventions, depression stigma, and utilization and cost of interventions.

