## Background

Depressive disorders are severe mental illnesses with overall prevalence rates, measured from point prevalence up to 12-month prevalence, in the range of 2.6–19.4% among children and adolescents (C&A) [1–7]. Rates rise in adolescence compared to childhood [8] and show a stronger female preponderance in adolescents [2, 6]. Depression in C&A has a marked negative impact regarding poor academic performance and social dysfunction and predicts adverse mental health outcomes such as recurrence of depressive symptoms, substance abuse, self-harm, suicidal ideation, and attempted and completed suicide [9–11]. Due to the high burden of depression for both personal and societal areas, early intervention and prevention of its onset are of utmost importance [12, 13]. Targeting subthreshold depression in particular is of enormous potential as subthreshold depression in adolescents is a substantial risk factor for the onset of major depression [14]. However, currently the vast majority of C&A with subthreshold depressive symptoms does not seek professional help and does not receive professional support. Barriers to help-seeking include poor mental health literacy, shame and stigmatization related to depression [15], but also symptoms of depression itself, such as feelings of worthlessness or guilt. Internet-based interventions present a promising approach to overcome these barriers, especially as various studies have shown that a high percentage of C&A use the Internet for health-related purposes (e. g. seeking health-related information and support communities; [16]). Internet-based interventions provide low-threshold access to evidence-based information, self-help tools, peer support, and professional counseling and could thus help in reaching target populations who might otherwise not seek treatment.

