### Randomization

Following the school-based baseline screening within the ProHEAD consortium, participants eligible for the E.motion trial will receive an e-mail including information about the trial and access details for the baseline assessment within the E.motion trial. After completing this assessment, participants will be randomized with equal probability (in a 1:1:1 ratio) to one of the three intervention groups. The assignment to the three conditions will be randomized, stratified for gender and school type. Randomization will be conducted externally and follow a permutated block design. Following randomization, participants will be contacted again via e-mail to be informed about their allocation to the respective intervention group and receive access details for the specific online programs. Blinding is not possible as the study assistants will be involved in delivering the interventions. However, the risk of a potential bias is considered minimal as the study outcome variables are exclusively based on self-report. For all treatment arms, the intervention will be discontinued at any time for participants who withdraw consent to participate in the trial.

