### Sample size calculation

We assume a small to medium effect (superiority of the two intervention groups over the control condition) on depressive symptomatology at postline after treatment as reported in meta-analyses on interventions for the prevention of depression in C&A [60]. Non-inferiority of the two active intervention groups is assumed. Repeated measures mixed models will be conducted (time*group interaction, alpha = 5%). Assuming a small to medium effect of *f* = 0.13, a lost-to-follow-up rate of 20%, and correlations of 0.2 among repeated measures, *n* = 363 individuals (*n* = 121 per group) need to be recruited for a test of the global hypothesis with 90% power. In case the ANOVA shows significant differences, post-hoc pairwise group comparisons can be conducted at a power of about 80% (Bonferroni correction) with the planned sample size.

Participants will be recruited within the ProHEAD consortium from the school-based sample of *N* = 15,000 screened C&A. Based on prevalence rates of approximately 5–12% of subthreshold depression in adolescents [14], 10% or *n* = 1500 of the screened C&A are expected to be eligible for inclusion in the trial. Thus, in order to meet the required sample size of *n* = 363, about 25% of eligible C&A would have to be willing to participate in the trial.

Criteria for the allocation of participants to the five individual ProHEAD trials are based on latest scientific evidence. However, this is the first time that the overall algorithm is applied on a consortium-wide basis simultaneously screening for various mental health problems. Therefore, an intermediate data analysis will be conducted following completion of 10% of the screening assessments (*N* = 1500) in order to determine the actual allocation ratio to the five ProHEAD trials and to adjust the screening algorithm if necessary.

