### Statistical analysis plan

All analyses will be conducted in accordance with intention-to-treat (ITT) principles, i.e. all randomized individuals will be included in the analysis [61]. In addition to the primary ITT analysis, per-protocol analysis will be conducted.

For the primary outcome, repeated measures mixed models (time*group interaction) will be conducted to test for differences in efficacy between the intervention groups. In case of statistically significant results, group differences will be investigated using post-hoc pairwise comparisons (Bonferroni correction). Secondary analyses using repeated measures mixed models will be performed on variables related to help-seeking behavior and depression stigma. In addition, repeated measures mixed models will be conducted to examine long-term group differences in PHQ-A scores at the six-month, one-year, and two-year follow-up timepoints, respectively. All analyses will include testing for interaction effects with study site (time*group*study site interaction).

Additionally, cost-effectiveness analyses and cost-utility analyses will be conducted. Cost-effectiveness analyses include the calculation of the ICER. The ICER indicates the additional cost for each additional (primary) outcome that has to be paid under routine care conditions. During these analyses, standard health economy techniques will be applied, such as bootstrapping techniques for estimating ICER variability, the calculation of cost-effectiveness acceptability curves (CEAC), and calculation of willingness-to-pay (WTP) criteria [62, 63]. In addition, a cost-utility study will be conducted that requires the transformation of longitudinal quality of life data (assessed with the KIDSCREEN-10) into preference measures, for the calculation of QALYs lost or gained during follow-up in order to calculate costs per QALY of the intervention.

Analyses will be performed using IBM SPSS Statistics and *p* values < 0.05 will be considered statistically significant.

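### The described models name neither stratification factor (gender, school type), and the role of the site interaction in the primary analysis is left open

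*Protocol article*

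**What the plan says.** Protocol article, Randomization: allocation is 1:1:1 ("participants will be randomized with equal probability (in a 1:1:1 ratio) to one of the three intervention groups"), in permuted blocks ("Randomization will be conducted externally and follow a permutated block design"), within strata: "The assignment to the three conditions will be randomized, stratified for gender and school type". Site is not named as a stratum, although participants "will be recruited at five study sites across Germany" (Abstract, Methods).

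Protocol article, Statistical analysis plan: "For the primary outcome, repeated measures mixed models (time*group interaction) will be conducted to test for differences in efficacy between the intervention groups". Gender and school type do not appear there, and no other covariate is named. The section then adds, for the primary and every other analysis: "All analyses will include testing for interaction effects with study site (time*group*study site interaction". It does not say whether this term is kept in the model that yields the primary result or is fitted separately, nor what follows if it is significant. The software is named (SPSS), but the type of sums of squares and the final model are not.

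Protocol article, Sample size calculation: power is given for the global time-by-group test and for the Bonferroni-corrected pairwise comparisons only.

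**The concern.** Blocking within strata makes the arms alike on gender and school type. The true sampling variance of the group contrast therefore excludes whatever the strata explain. A model without the strata still counts that part as residual noise, so its standard error is too large for the design and the test is conservative. The benefit of stratifying is then partly given up at the analysis stage.

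The site sentence raises a second question. A heterogeneity check in a five-site trial is ordinary. But if the three-way term stays in a factorial model with tests that weight sites equally, the time-by-group effect becomes an unweighted average over five sites. Its precision then depends on how uneven the sites are. One sentence thus allows two different primary tests.

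**Working it through.** **Inputs from the Protocol article.** Three groups, five sites, f = 0.13, correlation 0.2, alpha 5%, 20% loss, 363 recruited (121 per group), 90% power. **Assumptions, not in the document:** eight strata, the share of variance in change that the strata explain, and the site shares.

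1. *The plan's own figure.* For the time-by-group test with k = 3 groups and m = 2 time points, λ = f²·N·m/(1 − ρ), df1 = (k − 1)(m − 1) = 2, df2 = (N − k)(m − 1). With N = 303, λ = 0.0169 × 303 × 2/0.8 = 12.80 and power is 0.900. That is 101 per group, and 101 × 1.2 = 121.2, so 121 per group and 363 in total. The stated size is reproduced. A 20% loss from 363 leaves about 290 completers (0.8 × 363 = 290.4), with power 0.887.

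2. *Which variance matters.* With two time points and complete data, the time-by-group test is a comparison of within-person change. A stable difference in PHQ-A level between genders or school types cancels. Only differences in change between strata add noise, so the relevant quantity is R², the share of variance in **change** explained by the strata.

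3. *Cost of leaving out the strata.* Simulation of the global test on change scores: n = 288 (eight strata of 36), blocked 1:1:1 within stratum, 6,000 runs per setting. Both intervention arms were shifted by 0.44 SD of change. The squared SD of the three means is 0.44² × 2/9 = 0.043, close to the plan's f²·m/(1 − ρ) = 0.0169 × 2/0.8 = 0.042.

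| R² for change (assumed) | Type I error, unadjusted | Type I error, adjusted | Power, unadjusted | Power, adjusted |
|---|---|---|---|---|
| 0 | 0.045 | 0.047 | 0.896 | 0.896 |
| 5% | 0.044 | 0.050 | 0.885 | 0.897 |
| 10% | 0.038 | 0.053 | 0.897 | 0.919 |
| 20% | 0.025 | 0.054 | 0.904 | 0.946 |

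The simulation standard error is about √(0.05 × 0.95/6000) = 0.003 for type I error and √(0.9 × 0.1/6000) = 0.004 for power. At 5% the unadjusted type I error is therefore hardly distinguishable from nominal, given 0.045 at R² = 0. At 10% it is clearly lower.

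4. *Site term kept in the primary model, sites weighted equally.* With site shares w, the variance relative to the pooled contrast is (1/25)·Σ(1/w).
   - Equal sites: (1/25) × 25 = 1.00. Power with 290 completers is 0.887.
   - 30/25/20/15/10: (1/25)(3.33 + 4 + 5 + 6.67 + 10) = 29/25 = 1.16. Power is 0.832.
   - 40/30/15/10/5, a very uneven case: (1/25)(2.5 + 3.33 + 6.67 + 10 + 20) = 42.5/25 = 1.70. Power is 0.661.

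5. *The site test itself.* df1 = (3 − 1)(5 − 1)(2 − 1) = 8 over 3 × 5 = 15 group-by-site cells, about 290/15 = 19 completers per cell. Even for an interaction as large as f = 0.13, power with 290 completers is about 0.68. Reaching 90% would take about 460 completers, or 460/0.8 = 575 recruited.

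**The case against.** The strongest reply is that the strata point rests on silence. The article lists no covariates, random effects or covariance structure. It names the effect to be tested, and a covariate list is commonly left to a full analysis plan, which is not shown. This stands in part: the text does not exclude the strata. But the section does name model terms, including a further design factor, for all analyses. The models as described lack the two factors that constrained allocation.

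On site, the natural reading is an added heterogeneity check. The primary test is fixed first as time-by-group, and the sample size is built on that alone. Retaining the term, equal weighting and the site shares are suppositions. This stands, so the variance increase is conditional, and it is zero for equal sites.

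Four stronger readings may tempt a reader, and the document supports none of them:

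- *That it calls gender prognostic.* The Background says only that prevalence rates "show a stronger female preponderance in adolescents". That concerns who has the disorder, not who changes on PHQ-A among participants selected for scores of 5–9.
- *That site is used in place of the strata.* The text makes no such substitution, and a site interaction test is not wrong because site was not a stratum.
- *That strata explaining 5–10% of total PHQ-A variance would be like losing 5–10% of participants.* Stable level differences cancel in the time-by-group test.
- *That false positives are inflated.* Omission errs towards conservatism.

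**Conclusion.** The point holds as an inexpensive improvement, not as an error that undermines the trial. The design stratifies on gender and school type, and the described models carry neither. The resulting time-by-group test is unbiased and at most mildly conservative. Under the assumed 5–10% of variance in change, adjustment gains about 1 to 2 percentage points of power (0.897 − 0.885 = 0.012; 0.919 − 0.897 = 0.022). If the strata do not predict change, nothing is lost. The document gives no basis for choosing within that range.

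The site sentence needs its role stated, because it reaches the primary analysis. The variance increase (16% in the moderately uneven example) arises only if the term is retained, sites are weighted equally and site sizes differ. What does not depend on those assumptions is that an 8-df test is fixed for every analysis, lies outside the sample size calculation and has no stated consequence.

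**What to change.** In the section Statistical analysis plan:

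1. State that the primary and secondary mixed models include gender and school type, each with its interaction with time, as fixed effects. The time interactions matter: main effects alone would do little for the time-by-group test.
2. State that the time-by-group-by-site test is fitted in a separate, supportive heterogeneity model, and that its result does not alter the primary time-by-group result.

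The cost is wording and a few degrees of freedom. Both factors must be known to randomise, so no new data are needed, and the sample size does not change.

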### Organization, quality assurance, and data management

Research data will be collected in a pseudonymized manner by means of online questionnaires. Data quality will be ensured by conducting automatic validity and range checks at data entry. The confidentiality of participants is secured by providing unique study identifiers unrelated to the real name. All study-related data will be stored on secure servers at the principal investigator’s institution with frequent back-up procedures in place. Data will be stored for 10 years at the primary research institution. Data handling and access will follow German and European Union legal regulations concerning data protection and data security. The Coordination Center for Clinical Trials (KKS) Heidelberg will monitor study-related procedures at the five recruiting centers. Specifically, the recruitment of schools within the target regions and the recruitment of students within these schools will be monitored in order to ensure adherence to the study manual and documentation guidelines as well as equivalent procedures at all sites. In addition, an independent Data and Safety Monitoring Board (DSMB) as defined in ICH-GCP will assess the progress of the trial, data safety, and the clinical efficacy endpoints.

### Safety reporting

There is no obvious risk for participating C&A. The study does not involve any restriction to standard care. All participants will receive information on where to seek help for mental health problems within the ProHEAD consortium. In case of C&A reporting suicidal plans or suicide attempts, special emergency procedures will be put in place allowing immediate contact of the participant in order to assess risks and refer to appropriate care. Potential serious adverse events (SAE) will be reported to the local ethics committee, the DSMB, and the KKS.

### Dissemination

Trial results will be published in peer-reviewed international journals and will be presented at national and international conferences. Substantial protocol modifications will be communicated to the ethics committee, trial registry, DSMB, and all relevant parties.

## Discussion

This study represents the first RCT investigating efficacy and cost-effectiveness of two online interventions for C&A at risk for depression. To our knowledge, this is the first study, aiming at large scale, sustainable implementation of Internet-based indicated prevention of depression within an integrated infrastructure that aims at health promotion, prevention of clinical symptoms, and facilitating help-seeking. Research on the cost-effectiveness of such interventions is sparse as well and the results of the study will provide a strong basis for decision-making for stakeholders and policy makers in the field. Also, the trial will provide new insights into so far understudied aspects of E-mental health programs, such as potential negative effects of online interventions and user characteristics. Further, this RCT will overcome current shortcomings of available studies, with a particular focus on professional guidance by mental health professionals for participants and longer follow-up periods and provide an internationally consented, guided self-management tool which has been broadly used in adults with milder forms of depression in 11 different languages/countries already.

This RCT will advance the state of the art by bringing an established, guided, online-delivered self-management approach, which is well implemented into routine care, to the large population of unrecognized C&A with subthreshold depression being at risk of developing a depressive disorder.

In summary, the trial will: (1) significantly add to the existing evidence on Internet-based indicated prevention of depression in C&A at risk for the development of depression; (2) be the first study to investigate effects of Internet-based indicated prevention on help-seeking in C&A with subthreshold depressive symptoms; and (3) provide cost-effectiveness data on Internet-based indicated depression prevention.

### Trial status

The trial was registered at the German Register for Clinical Trials (DRKS) under the title “ProHEAD – Promoting Help-seeking using E-technology for Adolescents. Sub-project 4: Efficacy and cost-effectiveness of two online interventions for children and adolescents at risk for depression (E.motion trial)”, identification code: DRKS00014668. International trial-registration took place through the “international clinical trials registry platform” with the secondary ID S-086/2018.

The recruitment period for the trial will start in October 2018 and is predicted to continue until March 2020.

## Abbreviations

AHSQ: Actual Help-Seeking Questionnaire
AUDIT: Alcohol Use Disorders Identification Test
C&A: Children and adolescents
CBT: Cognitive-behavioral therapy
CEAC: Cost-effectiveness acceptability curves
CRAFFT-d: Car, Relax, Alone, Forget, Friends, Trouble
DRKS: German Register for Clinical Trials
DSMB: Data and Safety Monitoring Board
DSM-IV: Diagnostic and Statistical Manual of Mental Disorders, fourth edition
DSS: Depression Stigma Scale
GHSQ: General Help-Seeking Questionnaire
IASMHS: Inventory of Attitudes Toward Seeking Mental Health Services
ICER: Incremental cost-effectiveness ratio
iFD: iFightDepression
IIT: Investigator-initiated trial
INEP: Inventory for the assessment of negative effects of psychotherapy
ITT: Intention-to-treat
KIDSCREEN-10: Health-related quality of life measure for children and adolescents
KKS: Coordination Center for Clinical Trials
MRV: Mannheimer Modul zum Ressourcenverbrauch
PHQ-A: Patient Health Questionnaire-9 modified for Adolescents
QALY: Cost per quality-adjusted life year
RCT: Randomized controlled tial
SAE: Serious adverse event
SDQ: Strengths and Difficulties Questionnaire
SEED: Short Evaluation of Eating Disorders
WCS: Weight Concerns Scale
WTP: Willingness-to-pay
ZUF-8: German version of the Client Satisfaction Questionnaire
